#### Training Details

The exercise session will consist of approximately 5 minutes of warm-up, 30 minutes of accumulated exercise (not including rest periods), and cooldown (if necessary). The walking treadmill exercise prescription is individualized to each participant’s exercise capacity during baseline testing and their rate of progression. The protocol requires participants to accumulate a total of 30 minutes of walking with claudication pain. Neither rest time nor time spent exercising before pain onset will count toward the 30-minute goal. The patient will be encouraged to continue walking as far as they can, but will self-select when they require a rest break. Exercise and rest periods are repeated during each session until the minimum total of 30 minutes of walking time is reached each session. When a patient can walk 8-10 minutes at the initial workload, the grade will be increased by 0.5%, or the speed increased by 0.1 mph as tolerated, to ensure workload progression.

Subjects will be supervised by a trained exercise physiologist and will have continuous telemetry heart rate monitoring using the Polar heart rate monitor (Polar Electro). Fatigue will be assessed through rating of perceived exertion via the Borg 6-20 scale; blood pressure will be checked both before and after exercise as well as periodically during each exercise.

Each exercise training session will be documented with preexercise and postexercise vital signs, time of day beverage was consumed, total exercise time, and workload (ie, treadmill speed and grade) recorded. Body weight and dietary intake will be assessed on a weekly basis. All research team members working with the subjects will be blinded to the treatment intervention and every attempt will be made keep encouragement and workload adjustment standardized between subjects.

### Testing Methodology

#### Overview

The subjects and research staff conducting the testing will be unaware of group assignments. The primary investigator will know to which treatment group the subjects are randomized, since changes in plasma nitrate and nitrite will be used to determine beverage volumes and tolerance. Because of the potential for bias, however, the primary investigator will not be directly involved in collecting or analyzing any of the exercise performance or training data.

For all testing visits, participants will be advised to avoid exercise and consuming alcohol for 24 hours prior to the examination day. They will also be asked to avoid tobacco and caffeine for 3 hours prior to any testing or exercise visit.

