**Methods:**

A total of 30 subjects between 40 and 80 years of age with PAD who are limited by IC will undergo exercise training 3 days per week for 12 weeks (ie, 36 sessions). They will be randomized to either the EX+BR or EX+PL group where participants will consume a beverage high in inorganic nitrate (4.2 mmol) or a low-nitrate placebo, respectively, 3 hours prior to each training session.

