The hypothesis of this study is that subjects with peripheral artery disease with intermittent claudication (PAD+IC) who undertake regular consumption of a high-inorganic nitrate (4.2 mmol) supplement in conjunction with 12 weeks of supervised exercise training (exercise training plus beetroot juice [EX+BR]) will experience a greater clinical benefit in pain-free walking time (COT, 6-minute walk [6MW]) and PWT than those undertaking exercise and a placebo beverage (exercise training plus placebo juice [EX+PL]) alone. Specifically, the primary aim of this study is to determine group differences (EX+BR vs EX+PL) in the changes in the following:

Exercise capacity: pain-free walking time (COT), PWT, and maximal exercise capacity/peak oxygen uptake (VO_2peak_) during a maximal-graded cardiopulmonary exercise test (max CPX).Functional capacity: 6MW distance.

Secondary aims designed to provide mechanistic insight into the exercise outcomes include the following:

Gastrocnemius tissue oxygenation during max CPX testing via near-infrared spectroscopy (NIRS).Gastrocnemius muscle angiogenesis: capillaries per unit area and per muscle fiber, and relative fraction of type I, IIa, IIb, and IId/x fibers.Vascular health/function via brachial artery flow-mediated dilation, lower-limb blood flow via plethysmography, and pulse wave velocity (PWV) and reflection.

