## Methods

### Study Design

The NO-PAD trial is a pilot, randomized, double-blind, per-protocol design with four different assessment time points (see Figure 1). This study is registered with ClinicalTrials.gov (NCT01785524).

The first round of assessment will act as a baseline with no exercise intervention or supplementation. Following this, all participants will be randomized to groups consuming either a 70 mL (4.2 mmol nitrate) beetroot juice (Beet It, James White Drinks Ltd, Ipswich, UK) or an identical nitrate-depleted placebo. Participants will then repeat the baseline assessments, except for the muscle biopsy, but will consume their assigned beverage 3 hours prior to each visit.

Participants will continue consuming their beverage 3 hours prior to each of their 36 exercise training sessions. Periodically, subjects will be selected for unannounced blood draws at training visits to check plasma nitrate and nitrite concentrations. Post-exercise training, participants will complete the same assessments as the baseline visit while still acutely consuming their beverage before visits. Both groups will then stop consuming the beverage for at least 1 week prior to the final visit. The half-life of nitrate is 5-8 hours and as the supplementation protocol is three acute doses per week, a 1-week washout period should be sufficient to minimize any possible residual effect of the nitrate [41]. To maximize internal validity, study personnel, time of day, equipment, and order of testing will be consistent for each of the assessment time points.

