### Supplementation

Following initial screening and baseline testing, subjects will be randomized to consume either a high-nitrate-containing beetroot beverage or a low-nitrate placebo throughout the duration of the exercise training. Randomization should ensure the groups are initially equal within either the EX+BR or EX+PL intervention. Both groups will be instructed to consume one 70 mL bottle of beetroot juice (containing 4.2 mmol inorganic nitrate) 2.5-3 hours prior to every testing visit and training session between time point 2 and time point 3. The beetroot juice bottles will be identical in appearance and taste. The bottles will be color coded by a third party to ensure that the research staff remain blinded while providing the correct supplement to each participant.

Scheduled but unannounced blood draws will be performed throughout the study to confirm participants are conforming to their appropriate beverage allocations.

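### The volume-setting reason for unblinding the primary investigator contradicts the fixed dose, and the safeguard on that person does not reach the vascular and biopsy analyses

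*Protocol article*

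**What the plan says.** The Overview of Testing Methodology states that subjects and testing staff do not know the allocation but the primary investigator does, "since changes in plasma nitrate and nitrite will be used to determine beverage volumes and tolerance". Acknowledging a risk of bias, it then adds that "the primary investigator will not be directly involved in collecting or analyzing any of the exercise performance or training data".

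The beverage is specified in four other places:

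- Abstract, Methods: "participants will consume a beverage high in inorganic nitrate (4.2 mmol) or a low-nitrate placebo".
- Introduction, hypothesis: "regular consumption of a high-inorganic nitrate (4.2 mmol) supplement".
- Study Design: "70 mL (4.2 mmol nitrate) beetroot juice".
- Supplementation: participants are to "consume one 70 mL bottle of beetroot juice (containing 4.2 mmol inorganic nitrate") before every testing visit and training session between the second and third time points.

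The blood draws during training have their own stated uses. Study Design says: "Periodically, subjects will be selected for unannounced blood draws at training visits to check plasma nitrate and nitrite concentrations". Supplementation says: "Scheduled but unannounced blood draws will be performed throughout the study to confirm participants are conforming to their appropriate beverage allocations".

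**The concern.** Two things do not fit together.

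First, the article gives the setting of beverage volumes from plasma levels as a reason for unblinding, yet elsewhere the volume is one bottle for everyone. If volumes had in fact been adjusted, participants would not all have received the 4.2 mmol exposure named in the hypothesis, and the effect sizes carried into the planned confirmatory trial would belong to a different regimen.

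Second, the Overview recognizes that an unblinded investigator is a source of bias and then defines the remedy by type of data. Part of the secondary data lies outside that definition. Those outcomes are meant to explain the mechanism behind the walking results, and some of them involve a reading step after the visit.

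**Working it through.** No sample size, power or error-rate figure is involved. The check sets the sections side by side.

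**1. Is there a volume to determine?**

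| Place | Dose | Volume |
|---|---|---|
| Abstract, Methods | 4.2 mmol | not given |
| Introduction, hypothesis | 4.2 mmol | not given |
| Study Design | 4.2 mmol | 70 mL |
| Supplementation | 4.2 mmol | one 70 mL bottle |
| Testing Methodology, Overview | not given | to be set from plasma nitrate and nitrite |

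All four places that state a dose agree on it, and the two that state a volume agree on that too. No section gives a titration rule, a target plasma level or a range of volumes. Study Design uses the draws at training visits to check concentrations, and Supplementation uses them to confirm adherence to allocation. The section on nitric oxide bioavailability describes the sampling and assay around the maximal exercise test without linking the result to dosing. The fixed dose is therefore the clear reading, and the volume clause is the outlier.

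**2. Does anything else in the stated reason survive?** Yes. The clause also names tolerance, which can be monitored under a fixed dose. Checking that a participant's plasma levels match the assigned beverage may also need one person who knows the allocation, although the Overview does not offer that as its reason.

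**3. What does the bar cover?**

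- Primary outcomes: claudication onset time, peak walk time, peak oxygen uptake and 6-minute walk distance are all exercise performance data. Outside the bar: 0 of 4.
- Secondary aims: near-infrared spectroscopy is recorded during the maximal exercise test and is plausibly covered. Muscle angiogenesis and vascular function are not exercise performance or training data in any ordinary sense. Outside the bar: 2 of 3.

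**4. Does the blinding of other staff close that gap?** Only for data collection. The Overview blinds those who conduct the tests, and Training Details blinds those who work with the subjects. Biopsy tissue, however, is frozen, stored and measured after thawing (Gastrocnemius Muscle Biopsy). Flow-mediated dilation is calculated from recorded brachial images (Endothelial Function). These later steps are reading and analysis. The one person known to be unblinded is not kept out of them by the wording of the bar.

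**The case against.** The strongest reply is that the second part argues from silence. The article nowhere says that the primary investigator reads vascular images or biopsy sections. The sentence blinding the testing staff stands at the head of the section that contains both sets of procedures, and some vascular measures are derived by software. Who reads the slides is a detail that an article may leave to the full protocol. Much of this stands: no unblinded reading is documented. But the article does not merely omit the safeguard. It states one, gives the reason for it and sets its scope, and that scope can be judged as written.

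A second reply is that tolerance is half of the stated reason and fits a fixed dose. That also stands, and it limits the contradiction to the volume clause.

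A reader might go further and infer that per-protocol exclusions were open to unblinded judgment. The documents do not support this. The attendance rule in Overall Program and Attendance Requirements is numeric: 34 of 36 sessions, so 36 − 34 = 2 may be missed. It runs on session records, which are naturally training data and so fall under the bar. The other stated exclusion is withdrawal by the subject. No section gives this investigator a role in exclusions, and Results already reports arm sizes of 11 and 13.

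**Conclusion.** The point holds and is minor. The volume-setting rationale contradicts the fixed dose of one 70 mL bottle, while tolerance monitoring and a compliance check remain compatible with it. The bar on the unblinded investigator covers all four primary outcomes but, as worded, leaves out the later reading and analysis of two of the three secondary aims.

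This rests on two readings: that the repeated fixed dose is what was intended, and that vascular and biopsy measurements are not exercise performance or training data.

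It would be tempting to conclude that the double-blind claim fails or that the walking results are biased. Neither follows. Subjects, trainers and testing staff are blinded, and the investigator is barred from collecting or analyzing the walking data. No size of bias is claimed for any outcome.

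**What to change.** - In the Overview of Testing Methodology, delete the setting of beverage volumes as a reason for unblinding and state that the dose was fixed at one 70 mL bottle (4.2 mmol). If any volume was changed, report the changes by arm.
- If the unblinding served tolerance monitoring or the compliance check, give that as the reason.
- Widen the bar so that the unblinded investigator does not read or analyze any outcome, including vascular and biopsy data not yet analyzed.

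The cost is small: one clause reworded, one statement on volumes, and the loss of one person's input to the remaining vascular and biopsy analyses. Results says that data collection is complete and analysis is in progress, so the wider bar can still help. It does not say how much vascular or biopsy work is left. For any part already done, the report should state whether the reader knew the allocation.

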#### Maximal Cardiopulmonary Exercise Test

##### Overview

The maximal cardiopulmonary exercise test (CPX) with a 12-lead electrocardiogram and expired gas analysis will be conducted using a modified Gardner protocol. This protocol starts at 2.0 mph and 0.0% grade and increases by 2.0% grade every 2 minutes at each stage [42].

Prior to commencing the protocol, participants will be familiarized with the Borg rating of perceived exertion scale as well as the claudication pain scale. Resting measures of gastrocnemius tissue oxygenation, via NIRS, and oxygen consumption, via a metabolic cart, will be recorded.

Throughout the test, heart rate, blood pressure, NIRS, and rating of perceived exertion will be monitored. Assuming there are no adverse events, participants will walk on the treadmill until volitional exhaustion. These participants will likely be limited by leg claudication pain and, therefore, we expect to attain a VO_2peak_, rather than a maximum.

##### Measures of Pain-Free Walking Time and Maximal Exercise Capacity

The measure of pain-free walking time will be recorded as the total time walked prior to the onset of claudication pain. During the max CPX, participants will be instructed to inform a research team member when they first feel pain in their leg during exercise—this will be recorded as COT. PWT will be recorded as the total time (in seconds) that the participant walked on the treadmill. VO_2peak_ will be the average of the last 30 seconds of exercise.

##### Nitric Oxide Bioavailability Measurement (Plasma Nitrite Changes)

Prior to beginning the max CPX, a 20-gauge intravenous catheter will be placed in an antecubital vein. Approximately 5 mL of blood will be taken prior to the max CPX testing (Pre) and at 10 minutes following exercise termination (Post). Samples will then be separated into five 1 mL Eppendorf tubes containing 5 µL heparin (1-1000 U/mL) and centrifuged at 5000 g for 3-4 minutes [26]. Afterward, the plasma will be removed into five separate tubes, snap-frozen in liquid nitrogen, and stored at -80°C until analysis.

All NO metabolite concentrations will be measured within 30 minutes of defrosting by chemiluminescence using the NOA 280 nitric oxide analyzer (Sievers Instruments) as per the manufacturer’s instructions. The reductant used for nitrite analysis will be potassium iodide in acetic acid, which has the reduction potential to convert nitrite to NO; this reductant is insufficient to reduce any higher oxides of nitrogen such as nitrate and, thus, is relatively specific for nitrite. To obtain concentrations of total plasma nitrogen oxides, we will use the same apparatus with a stronger reductant, vanadium chloride in 1 M HCl, at 94°C. This reduces the sum of all nitrogen oxides with an oxidation state of +2 or higher, which is predominantly nitrate (µM), but also includes both nitrite (nM) and nitrosothiols (nM).

##### Tissue Oxygenation Measurement (Near-Infrared Spectroscopy)

NIRS has been shown to be a reproducible and reliable method to determine tissue oxygen stores in human skeletal muscle tissue [38]. The NIRS PortaMon device (Artinis Medical Systems) is a noninvasive portable tool for measuring tissue oxygenation. It works by emitting near-infrared light wavelengths of 760 nm and 850 nm that correspond to the absorption spectra of hemoglobin (Hb) and deoxygenated Hb, respectively. Depending on the oxygenation status of the tissues (ie, how much oxygenated vs deoxygenated Hb is present), the resultant spectra will change and the light fraction will be captured by a detector on the device itself [39]. This technique provides continuous snapshots of the muscle tissue oxygenation as well as percent oxygen saturation.

The tissue oxygenation will be assessed utilizing the NIRS device to obtain an index of fractional oxygen extraction—[deoxy(Hb + myoglobin)]—and percent oxygen saturation at rest at the beginning of the exercise test and continuously monitored throughout the max CPX and recovery period [26].

#### Vascular Function

##### Overview

For the vascular testing visit, subjects will be instructed to withhold all medications and consume no food for 8 hours prior to the exam. All vascular testing will be performed between 8 am and 11 am in a temperature-controlled room following 10-15 minutes of quiet relaxation.

##### Endothelial Function (Brachial Artery Flow-Mediated Dilation)

Endothelial dysfunction is a precursor to the development of atherosclerosis and an independent predictor of cardiovascular events and clinical outcomes [43]. Brachial artery flow-mediated dilation is the most commonly used noninvasive measure for the assessment of endothelial function [44]. This technique relies on the reactive hyperemic response where there is an increase in arterial blood flow following a period of ischemia (ie, occlusion). The dilation of the artery—typically the brachial artery is imaged—represents, in part, the NO-mediated arterial response to sheer stress [43,45]. All imaging will be performed at the brachial artery of the left arm with the subject in a supine position, with the forearm extended and slightly supinated. All image captures will be r-wave triggered. Two 10-second video-captures of the brachial artery will be obtained at baseline (resting), and then 2 minutes of continuous imaging will be recorded following 5 minutes of distal forearm occlusion (reactive hyperemia). Absolute and relative changes in brachial artery diameter will be calculated as follows:

Absolute and relative changes in brachial artery diameter = (peak posthyperemia diastolic diameter − baseline diastolic diameter)/baseline diastolic diameter × 100 (1)

##### Vascular Stiffness

Central blood pressures—the pressures by which the internal organs are perfused—have been shown to be strongly related to clinical outcomes [46]. A specially designed brachial cuff will be utilized to capture brachial systolic and diastolic pressure as well as the pulse waveform. The SphygmoCor software version 8.0 (AtCor Medical) will then use a validated generalized transfer function to derive central diastolic and systolic blood pressure, mean arterial pressure and pressure product along with the pressure augmentation (ΔP) due to wave reflection, and the pressure augmentation index (AIx):

AIx = ΔP/pulse pressure × 100 (2)

To capture PWV, sequential measurements of arterial pressure waves will be taken at the carotid artery, using applanation tonometry, and femoral artery, using a specialized thigh cuff. The surface distances from the sternal notch to the carotid and femoral sites will be measured and input into the software for calculation of the PWV. Pressure wave transit times to each site will be measured using the foot-of-the-wave method:

Distance of pulse wave (DPW) = sternal notch distance to femoral artery − carotid artery distance to sternal notch (3)

Carotid − femoral PWV = DPW/transit time(s) (4)

##### Ankle-Brachial Index

The ankle-brachial index (ABI) is the ratio of blood pressure in the feet in comparison to the arms and is linked with mortality and morbidity rates [47,48]. Measurements will be obtained on both the left and right side of each subject. A 5-7 MHz handheld Doppler probe coupled with a BP cuff—positioned proximal to the probe—will be used to detect blood flow through the arteries. On each arm, the brachial artery will be occluded at the biceps using an appropriately sized BP cuff, while the Doppler probe will be placed over the brachial artery to detect blood flow. An additional cuff will be placed approximately 3 cm above the medial malleolus in order to occlude the anterior tibial (AT) artery. The AT artery bifurcates in the foot into the dorsalis pedis (DP) and the posterior tibialis (PT) arteries, so both the DP and PT arteries will be measured separately via Doppler after occlusion of the AT artery using the BP cuff. The average of the least two separate measurements will be taken at each artery. The ABI value will be calculated by dividing the higher average DP or PT value from each side by the highest average radial artery value obtained from either side [27].

##### Lower-Limb Blood Flow

Following the ABI procedure, the participant will be kept supine throughout the plethysmography measurements. Lower-limb blood flow will be assessed both at rest and following reactive hyperemia via the use of a Hokanson A16 mercury-in-silastic strain gauge plethysmograph (Hokanson Inc). Initial setup requires the patient to lie supine, with the legs elevated slightly above the level of the heart to facilitate venous emptying. Two BP cuffs will be placed on the upper thigh of the leg to be assessed: one will be used for arterial occlusion and one for venous occlusion. A mercury-in-silastic strain gauge will be placed around the widest part of the calf to allow for the indirect measurement of blood flow via changes in lower-limb diameter. Resting measures will be acquired by inflating and deflating the venous occlusion thigh cuffs to approximately 50 mmHg (ie, just above venous pressure) every 10 seconds for five cycles. During inflation, the mercury-in-silastic strain gauge will be placed under stress, which will then be graphically represented as a pressure response curve on the Hokanson A16 machine. The average of three resting measures will be used as the baseline arterial inflow measure. Following 5 minutes of rest, the thigh cuff will be inflated to 30 mmHg above systolic pressure to induce arterial occlusion for 5 minutes. Upon release of the occlusion cuff, the same procedure used for resting measures will be initiated whereby the venous occlusion cuff will be inflated and deflated to create a pressure response curve for blood flow following reactive hyperemia [17].

